#### Study Procedures

##### Randomization

Following informed consent and the baseline assessment (discussed later), we will use a web-based system to randomize women (1:1) to the *i.ARTs* intervention arm (n=90) or to the standard-of-care control arm (n=90). Neither participants nor researchers will be blind to study condition. Women in the control arm will receive standard of care as it exists at the time of LAI ART roll out: providers will offer women information about LAI ART and may strongly suggest which option she should choose. Women who participated in the focus groups will not be eligible for inclusion.

Women in the intervention arm will use *i.ARTs* as part of their regular participant visit. While the complete content of *i.ARTs* will be finalized in phase 2, the web-based *i.ARTs* app will guide WWH through the following activities: (1) provide education on different ART modalities, (2) utilize value clarification methods to guide women in ranking the prominence of relevant barriers and facilitators that may impact adherence to various ART modalities, (3) collect information on participant health history, (4) generate a suggested ART modality based on previous steps, (5) assist WWH in developing questions for their health care providers, and (6) generate an individual profile description as well as individualized suggestions to support adherence based on the modality selected (eg, a woman may be profiled as having transportation challenges; *i.ARTs* would suggest solutions—arranged transportation or transportation vouchers—that the clinic could employ to address these challenges). Participants will take a printout of this profile to their clinic visit with their provider. Intervention arm participants will receive US $15 for *i.ARTs* use.

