##### Assessments

All women enrolled in the study will complete a baseline survey following informed consent and a follow-up survey immediately after their clinical visit. Surveys will be administered on tablets in a private room within the clinic and will use REDCap for data collection. Each survey will take approximately 25 minutes to complete, and women will receive US $25. Survey measures are described later and in Table 2.

A subsample of 20 intervention (*i.ARTs*) arm women and 10 providers will be randomly chosen to participate in an exit interview. This interview will occur either at the baseline visit or up to 1 month after *i.ARTs* use at the participant’s convenience. We will select every fourth woman in the intervention arm to complete the exit interview. Providers will be selected based on the number of *i.ARTs* participants they served in the first year of the pilot (we will randomly select 10 providers from all providers who serve above the median number of *i.ARTs* clients, which ensures that providers will have sufficient experience with the tool to provide feedback) and exit interviews with providers will be conducted in the final 3 months of data collection. These interviews will focus on patient and provider experiences with *i.ARTs* acceptability, feasibility, and usability, and the most useful ways to improve its integration into clinical practice. This will also include discussions of how women shared the results from the patient decision aid with their provider. Exit interviews will take approximately 30 minutes and participants will be provided US $30 in compensation.

The study will also use all 180 participants’ electronic medical records (EMRs) to assess the impact of the intervention on clinical outcomes (Table 2). The informed consent process will include the EMR abstraction release form and detailed information about the data abstraction process. Study staff will abstract data on viral suppression (all women), ART modality, clinic attendance (all women), and medication refill data (women on oral ART) from EMRs into a REDCap database. Abstraction will include data from 1-year prebaseline to 6 months postbaseline. This timeline is based on the frequency of HIV clinic visits (ie, approximately every 3 months) to ensure that women have at least one visit in the follow-up period.

**Table 2 table2:** *i.ARTs*^a^ pilot study measures in phase 3.

Outcomes			Description of measures

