**Primary**			Assessed after *i.ARTs* use among women using i.ARTs (n=90)
	Feasibility	Adaptation of Thabane et al’s [59] framework [60,61] for assessing pilot studies: Process, Resources, Management, Science	
	Acceptability and usability	Acceptability [62] and CSQ-8^b^ [63] to measure satisfaction with *i.ARTs*; exit interviews about *i.ARTs* features/protocol [62]	
**Secondary**			Assessed in baseline survey and postvisit survey for all women (n=180)
	Decisional conflict	Decisional Conflict Scale (16 items) [52]; satisfaction with the chosen method [64]	
**Tertiary**			Assessed 1-year prebaseline, at baseline, 3 months, and 6 months (all women; n=180)
	Viral suppression	Viral suppression, defined as viral load below limit of detection per assay used	
	Medication refills	Missed doses; report of medication refills/pharmacy pick up (WWH^c^ on oral ART^d^)	
	Clinic attendance	Missed or cancelled medical visits (<2 visits in a 6-month period for oral ART; missed monthly visit for LAI^e^ ART)	
	ART modality	Adoption of LAI among patients who are virally suppressed	
**Moderators**			Assessed at baseline
	Sociodemographics	Race/ethnicity, age, housing stability, education, employment, income, distance from clinic, relationship status, children	
	Depression/anxiety	PHQ-8^f^ (depression) [65]; GAD-7^g^ [66]	
	Substance use	ASSIST^h^ [67], an 8-item measure of problematic substance use	
	Stigma/discrimination	MDS^i^ to measure racial discrimination [68]; HIV-related stigma	
	Self-efficacy	HIV-ASES^j^ [38]	
	ART-related knowledge	Adaptation of Feldman’s [69] scale of oral ART knowledge; BMQ^k^ [70]	

^a^*i.ARTs*: i.ART+support.

^b^CSQ-8: 8-item Client Satisfaction Questionnaire.

^c^WWH: women with HIV.

^d^ART: antiretroviral therapy.

^e^LAI: long-acting injectable.

^f^PHQ-8: 8-item Patient Health Questionnaire.

^g^GAD-7: 7-item General Anxiety Disorder scale.

^h^ASSIST: Alcohol, Smoking and Substance Involvement Screening Test.

^i^MDS: 10-item Multiple Discrimination Scale.

^j^HIV-ASES: HIV Treatment Adherence Self-Efficacy Scale.

^k^BMQ-18: 18-item Beliefs and Medicines Questionnaire.

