#### Study Outcomes and Measures

All study outcomes are summarized in Table 2. *Primary outcomes* include *i.ARTs feasibility, acceptability,* and *usability.* To assess feasibility, we will adapt Thabane et al’s [59] framework [60,61]. For *acceptability and usability,* we will use the 8-item Client Satisfaction Questionnaire (CSQ-8) to assess participants’ attitudes, burden, ethics, coherence, opportunity cost, perceived effectiveness, and self-efficacy [63]. The *secondary outcome* is ART-related decisional conflict, a 16-item scale scored from 0 to 100 [52]. Scores of 0-25 are associated with “implementing decisions” and scores of 37.5-100 are associated with “decision delay/feeling unsure.” *Tertiary outcomes* are exploratory, and consist of information extracted from EMRs, including viral suppression at the most recent visit in the prior 6 months, ART modality, medication refills (oral ART), and clinic attendance in the prior 6 months.

In addition to the outcomes, the baseline survey will measure moderators associated with adherence, including sociodemographics, depression, anxiety, substance use, HIV-related stigma and discrimination, self-efficacy, and ART-related knowledge.

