#### Analysis

The primary outcomes of feasibility, acceptability, and usability will be assessed descriptively. We will compare ART-related decisional conflict, clinic attendance, viral suppression, and medication refills between and within the 90 women in each arm (baseline vs postvisit surveys and EMR data at 3 and 6 months). For normally distributed data, we will first use *t* tests to compare the 2 arms and then use regression methods to develop a multivariable model of the outcome, with arm membership as the principal covariate, while controlling for the moderators listed in the previous sections and in Table 2. For nonnormally distributed data, we will employ chi-square tests and logistic regression; distributional properties of the outcome will determine the type of logistic regression (eg, binary, multinomial, or ordinal logistic regression models). We note that these are examples and the final approach will be determined based on the distribution of the data.

The primary analysis will use an intent-to-treat approach with the use of *i.ARTs* as a 1-time exposure, with α=.05, and 2-sided tests. The number of moderators included in the regression model will be used to make a Bonferroni adjustment to the α value. A secondary efficacy analysis will explore actual treatment taken. Our exploratory tertiary outcomes of viral suppression, clinic attendance, chosen ART modality, and medication refills will compare both between and within *i.ARTs* and control arm women (ie, baseline and postvisit surveys and EMR data at 3 and 6 months); we will also examine these outcomes for women who do not change regimens. We will use prebaseline EMR data to control for previous viral load. We will also compare how many women in each arm change modalities postbaseline to assess *i.ARTs’* accuracy in identifying which HIV treatment modality is the best match. Sensitivity analyses will determine whether assumptions associated with each model are defensible.

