### Expected Challenges

As this study is set in real-world clinical settings, we expect challenges to incorporating *i.ARTs* delivery into existing clinical workflows. These include considerations such as available space for participants to complete *i.ARTs*, tech support for the computerized tool and printout, staffing resources, and limited clinician time with each patient to discuss the decision aid results. The study team will work with the clinic staff to determine how to ensure efficient delivery of *i.ARTs* in the clinical setting. Exit interviews will be used to collect data on these challenges to inform further scale-up or dissemination efforts of *i.ARTs* outside of the Miami-based clinic*.*

As LAI ART is being administered in a real-world setting, participating clinicians are subject to existing, and possibly changing, FDA approvals. While phase 3 trials are currently testing LAI ART for nonadherent patients, *the FDA-approved LAI ART formulation is only for virally suppressed patients*. To ensure *i.ARTs* incorporates all relevant drivers of ART use for all women, we aim to include nonadherent women in aim 3, pending FDA approval. If FDA approval only exists for virally suppressed WWH when aim 3 starts, then we will limit the pilot test to that population. Should FDA approval for nonadherent patients begin in the middle of the pilot, we may adjust eligibility criteria to ensure a standard participant population throughout the pilot period. The study team will carefully monitor developments in ART treatment technologies and adapt accordingly. In addition, LAI ART was initially approved as a monthly injection, and the US FDA has approved a bimonthly (ie, every 8 weeks) formulation of LAI ART. This may also affect women’s preferences as the study is rolled out.

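### Clinic attendance and refills are scored by the ART modality a woman takes after randomisation, so a difference in LAI uptake distorts both between-arm comparisons

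*Protocol article*

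**What the plan says.** The tertiary block of Table 2 (Assessments) defines clinic attendance as missed or cancelled visits, with a threshold that depends on treatment: "<2 visits in a 6-month period for oral ART; missed monthly visit for LAI" ART. The text of Assessments sets the populations for abstraction: "clinic attendance (all women), and medication refill data (women on oral ART) from EMRs". Study Outcomes and Measures repeats the restriction, listing "medication refills (oral ART), and clinic attendance in the prior 6 months".

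Modality is decided after randomisation. Under Randomization, one function of the tool is to "generate a suggested ART modality based on previous steps", and Table 2 lists modality as an outcome in its own right: "Adoption of LAI among patients who are virally suppressed".

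The Analysis section compares attendance and refills between and within the 90 women in each arm, and states an intent-to-treat approach. It adds a secondary analysis by actual treatment taken and, for the tertiary outcomes, says that "we will also examine these outcomes for women who do not change regimens". Expected Challenges notes that "the US FDA has approved a bimonthly (ie, every 8 weeks) formulation of LAI ART".

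**The concern.** The yardstick for attendance, and the denominator for refills, both depend on something the intervention may change. A woman on oral ART is judged on about two visits in six months, and a woman on monthly LAI on about six. If the arms differ in LAI uptake, the arm with more LAI users carries more opportunities to fail, even when every woman is equally reliable at each visit.

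For refills, LAI users drop out of the analysis set. If i.ARTs changes how many women take LAI, or which women do, the two oral-ART subsets are no longer comparable by randomisation. The non-switcher and actual-treatment analyses also select on behaviour after randomisation, so neither restores the randomised comparison.

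At stake is the reading of the adherence signals from this pilot. The abstract names attendance and refills among the associations to be evaluated, and an artefact could be taken for harm or benefit.

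**Working it through.** **The plan's own figure.** The protocol gives no numerical assumption for attendance or refills. Its one explicit calculation, 80% power for decisional conflict with 90 per arm, reproduces closely: SD = √((16² + 18²)/2) = 17.03, effect = 7/17.03 = 0.411, power 78.3% by the t distribution. It does not bear on this point.

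**Inputs from the protocol.** HIV clinic visits are about every 3 months, so about 2 in 6 months. The LAI rule is monthly, so about 6 in 6 months. There are 90 women per arm.

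**Assumed inputs.** The per-visit miss probability *m* is the same on both modalities. LAI uptake is *u*. An LAI user fails if she misses any visit.

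**Attendance.** Failure over *k* visits = 1 − (1 − m)^k.
- At m = 0.10, oral (k = 2): 1 − 0.9² = 0.190.
- At m = 0.10, monthly LAI (k = 6): 1 − 0.9⁶ = 0.4686.
- Arm failure = u × LAI + (1 − u) × oral.
- Control, u = 0.15: 0.15 × 0.4686 + 0.85 × 0.190 = 0.2318.
- i.ARTs, u = 0.35: 0.35 × 0.4686 + 0.65 × 0.190 = 0.2875.
- Artefact = 0.20 × (0.4686 − 0.190) = 0.0557, or 5.6 points against i.ARTs with no true effect.

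**Sensitivity of the attendance artefact.**

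| Assumptions | LAI minus oral failure | Artefact |
|---|---|---|
| m = 5%, uptake gap 10 points, 6 LAI visits | 0.2649 − 0.0975 = 0.1674 | 1.7 points |
| m = 15%, uptake gap 30 points, 6 LAI visits | 0.6229 − 0.2775 = 0.3454 | 10.4 points |
| m = 10%, gap 20 points, 4 LAI visits | 0.3439 − 0.190 = 0.1539 | 3.1 points |
| m = 10%, gap 20 points, 3 LAI visits | 0.271 − 0.190 = 0.081 | 1.6 points |
| Any m, equal uptake | not relevant | 0 |

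The artefact also vanishes if LAI users are more reliable at each visit: q⁶ = 0.9² gives q = 0.9^(1/3) ≈ 0.965, against 0.90 on oral ART.

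**Effect on a test.** With uptake of 10% v 30%, 6 LAI visits and miss rates of 20%, 10% and 5%, the artefact is 7.6, 5.6 and 3.3 points. A nominal two-sided 5% test with 90 per arm then rejects in about 17%, 14% and 10% of trials.

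**One rule for all is not enough.** If the oral rule (fewer than 2 visits) is applied to everyone, the bias reverses. At m = 0.10 and uptake of 10% v 30%, failure is 17.1% in control and 13.3% with i.ARTs.

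**Refills.** Uptake of 10% v 30% leaves 90 × 0.9 = 81 and 90 × 0.7 = 63 women, not 90 and 90. To show selection, take 35% poor adherers in an arm. This borrows the national non-adherence figure from Power Analysis and Sample Size; the trial population may differ.
- If 20% of good and 50% of poor adherers take LAI, the adherent share of the oral subset is (0.65 × 0.8)/(0.65 × 0.8 + 0.35 × 0.5) = 0.520/0.695 = 74.8%.
- With those uptakes exchanged it is 0.325/(0.325 + 0.280) = 53.7%.
- With uptake unrelated to adherence it stays at 65%.

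No woman's refill behaviour changes in any of these cases.

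**The case against.** The strongest reply is that these outcomes are tertiary and labelled exploratory. The primary outcomes are descriptive and confined to the intervention arm, the sample size rests on decisional conflict, and viral suppression is collected in all women under one definition that does not depend on modality. All of this stands, and it limits the severity.

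Several stronger readings are tempting but not supported:

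- **The measure is biased against i.ARTs.** This needs higher LAI uptake with i.ARTs. The Introduction describes the tool as finding the option that fits a woman's preferences, not as promoting LAI, and control providers also give LAI information and may strongly suggest an option. Uptake could rise, fall or be equal.
- **Every woman on the 8-week formulation would be scored as failing.** That would give artefacts of roughly 7 to 27 points, but only if all LAI users were on that schedule and flagged for visits never booked. The lead wording concerns missed or cancelled visits, and Expected Challenges promises to adapt as treatments develop. What remains is that the monthly wording and the 8-week formulation must be reconciled.
- **The refill subset is selected because LAI is limited to suppressed women.** Expected Challenges would restrict the pilot to suppressed women if the approval stays so limited, which removes that mechanism at entry. Selection by preference and barriers remains possible, in an unknown direction.
- **The add-on analyses break intent to treat.** They are presented as additional or secondary, not as the intent-to-treat analysis. They simply cannot repair it.

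It is also fair that Table 2 does not say how several LAI visits are combined. The any-miss reading in the calculation is an assumption.

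**Conclusion.** The concern holds in a conditional form. The protocol fixes an attendance rule and a refill population that depend on modality after randomisation, then compares both by arm. If LAI uptake differs between arms, the attendance comparison is distorted. If i.ARTs changes who takes LAI, the refill comparison is not a randomised one.

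The attendance artefact is 5.6 points at a 10% miss rate and 15% v 35% uptake, and about 1.7 to 10.4 points over 5–15% miss rates and 10–30 point uptake gaps. It is smaller with fewer LAI visits and reverses if i.ARTs lowers uptake. These sizes rest on assumed miss rates and uptake, equal reliability per visit on both modalities, and an any-miss rule for LAI. The documents supply none of these. For refills, neither size nor direction can be predicted.

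Severity is moderate. The interpretation of two exploratory outcomes is affected. The primary outcomes, the sample size and the viral suppression definition are not.

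**What to change.** 1. **Attendance.** In all 180 women, use visits kept divided by visits scheduled after baseline, each woman scored against the schedule in her own EMR. State a rule that keeps women with no scheduled visit in the analysis, for example counting them as not retained, so that disengaged women are not dropped. With equal per-visit attendance among women who have scheduled visits, the expected ratio does not depend on LAI uptake.
2. **Refills.** Replace or supplement the oral-only outcome with the proportion of follow-up days covered by dispensed oral ART or by an injection given on its recorded schedule, in all 180 women.
3. **Analysis.** Compare both by randomised arm. Label the oral-only, no-regimen-change and actual-treatment-taken analyses as descriptive, not as randomised between-arm effects.
4. **Wording.** Reconcile the monthly rule in Table 2 with the 8-week formulation acknowledged in Expected Challenges. Scoring against each woman's recorded schedule does this without naming an interval.

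The cost is revised outcome wording and a little more abstraction (scheduled visit dates and injection dates) from records the study already plans to abstract.

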#### Study Outcomes and Measures

All study outcomes are summarized in Table 2. *Primary outcomes* include *i.ARTs feasibility, acceptability,* and *usability.* To assess feasibility, we will adapt Thabane et al’s [59] framework [60,61]. For *acceptability and usability,* we will use the 8-item Client Satisfaction Questionnaire (CSQ-8) to assess participants’ attitudes, burden, ethics, coherence, opportunity cost, perceived effectiveness, and self-efficacy [63]. The *secondary outcome* is ART-related decisional conflict, a 16-item scale scored from 0 to 100 [52]. Scores of 0-25 are associated with “implementing decisions” and scores of 37.5-100 are associated with “decision delay/feeling unsure.” *Tertiary outcomes* are exploratory, and consist of information extracted from EMRs, including viral suppression at the most recent visit in the prior 6 months, ART modality, medication refills (oral ART), and clinic attendance in the prior 6 months.

In addition to the outcomes, the baseline survey will measure moderators associated with adherence, including sociodemographics, depression, anxiety, substance use, HIV-related stigma and discrimination, self-efficacy, and ART-related knowledge.

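### The 6-month look-back for viral suppression and clinic attendance does not fit the 3-month assessment, and follow-up sized for one visit does not fit a two-visit attendance rule

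*Protocol article*

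**What the plan says.** Study Outcomes and Measures lists the tertiary, exploratory outcomes taken from the electronic medical record (EMR). Two of them carry a look-back: "viral suppression at the most recent visit in the prior 6 months" and "clinic attendance in the prior 6 months". ART modality has none, and none is clearly attached to refills.

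Table 2 gives the timing of the tertiary outcomes as "Assessed 1-year prebaseline, at baseline, 3 months, and 6 months (all women; n=180". The Analysis section compares the arms on "baseline vs postvisit surveys and EMR data at 3 and 6 months". Month 3 is therefore a comparison point in its own right.

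The Assessments section sets the extent of the data: "Abstraction will include data from 1-year prebaseline to 6 months postbaseline". It bases this length on "the frequency of HIV clinic visits (ie, approximately every 3 months" and gives the purpose as "to ensure that women have at least one visit in the follow-up period". Table 2 then flags poor attendance as "<2 visits in a 6-month period for oral ART; missed monthly visit for LAI" ART.

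Women are approached at a regular clinic visit (Setting, Participants, Recruitment, and Enrollment) and randomised after consent and the baseline survey (Randomization). The article prints no shorter look-back for month 3, no exclusion of earlier visits, and no statement on whether the recruitment visit counts.

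**The concern.** Two pairs of stated rules do not fit together.

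- **Look-back and assessment time.** A 6-month look-back applied 3 months after baseline takes in data from before the intervention. Such data cannot show an effect of the decision aid, so using them as outcomes pulls the arms together.
- **Length of follow-up and attendance threshold.** The record window is justified as long enough for one visit, but a woman on oral ART needs two to avoid being classed as a poor attender.

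At stake is the preliminary evidence on clinical outcomes. The Abstract names viral suppression and clinic attendance among the things the trial will evaluate, and the Power Analysis section says the trial can detect basic differences on the tertiary outcomes. A null month-3 result could reflect the window rather than the intervention. Attendance on oral and on injectable ART is also scored by different rules. If the decision aid changes uptake of the injectable, an error confined to the oral rule need not be equal in the two arms.

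**Working it through.** **Inputs from the article:** look-back 6 months; assessments at months 3 and 6; abstraction ends at month 6; visits about every 3 months; recruitment at a clinic visit (time 0); oral-ART threshold of 2 visits in 6 months.

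**Step 1: the plan's own figure.** With a constant gap g (months), the number of later visits by month 6 is floor(6/g). This is 2 for g = 2.5 or 3.0, and 1 for g = 3.01, 3.25, 3.5 or 4.0. The claim of at least one visit holds throughout.

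**Step 2: the windows.** An assessment at month t with a 6-month look-back covers t − 6 to t.

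- Month 3: −3 to +3, of which half precedes randomisation.
- Month 6: 0 to 6, none of which precedes it.

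**Step 3: viral load at month 3.** The number of later visits by month 3 is floor(3/g), which is 1 for g = 2.5 or 3.0 and 0 for any g above 3.0. When it is 0, the most recent visit is the recruitment visit. A viral load taken that day cannot reflect a treatment choice made that day.

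**Step 4: attendance at month 3.** With gaps of about 3 months, at most one later visit falls in months 0 to 3. The two-visit rule can be met at month 3 only by counting the recruitment visit or earlier ones.

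**Step 5: attendance at month 6.** The second later visit is due at 2 × 3 = 6.0 months, the last day of abstraction. From Step 1, a gap of 3.01 months already gives a count of 1, which fails the rule. If the recruitment visit counts, the total is 2 and she passes.

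**Step 6: size.** The article gives no distribution of visit gaps, so the following is assumed: independent normal gaps with mean m and SD s (months). Then

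- P(no later visit by month 3) = Φ((m − 3)/s)
- P(second later visit after month 6) = Φ((2m − 6)/(s√2))

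For m = 2.76 (12 weeks) and s = 0.25 these are Φ(−0.96) = 17% and Φ(−1.36) = 9%. For m = 3.25 and s = 0.25 they are Φ(1.00) = 84% and Φ(1.41) = 92%.

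| Mean gap | SD 0.25: month 3 / month 6 | SD 0.50 | SD 0.75 |
|---|---|---|---|
| 12 weeks | 17% / 9% | 32% / 25% | 37% / 33% |
| 3.00 months | 50% / 50% | 50% / 50% | 50% / 50% |
| 3.25 months | 84% / 92% | 69% / 76% | 63% / 68% |

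If the recruitment visit counts, the month-6 attendance figure is about 0% in every cell.

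**Step 7: dilution at month 3.** If a share f of women in each arm contribute pre-intervention values, observed difference = true difference × (1 − f). The article states no target difference for viral suppression, so take 15 points purely as an illustration:

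- f = 17%: 15 × 0.83 = 12.45 points
- f = 50%: 15 × 0.50 = 7.5 points
- f = 84%: 15 × 0.16 = 2.4 points

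**The case against.** The strongest reply is that the look-back appears once, in a summary sentence tied to no assessment time. It fits baseline (−6 to 0) and month 6 (0 to 6) exactly, and a condensed article may leave visit windows to the full protocol or analysis plan. On attendance, Table 2 names the measure as missed or cancelled visits, and a woman whose second appointment falls shortly after month 6 has missed nothing. The provider encounter on the recruitment day also follows randomisation, so it could legitimately count, and the month-6 error then disappears. Finally, these are exploratory outcomes in a pilot. The primary outcomes are descriptive, and the sample size rests on decisional conflict measured by survey, so neither depends on record windows.

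Much of this stands. It limits the severity, it makes the month-6 attendance point conditional, and the percentages above are only as good as the assumed gaps. The model also ignores women who start the injectable, whose monthly visits under Table 2 make a missing month-3 result less likely.

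It does not remove the month-3 problem. The look-back and the month-3 comparison are both stated, and followed as written they use pre-intervention data. Adjusting for earlier viral load, as the Analysis section plans, is no cure, because for the affected women the outcome and the covariate may be the same measurement.

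A reader might infer more than the documents support:

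- **That all record-based outcomes are affected.** ART modality has no stated look-back, and none is clearly attached to refills.
- **That month-6 viral suppression is contaminated.** Its window is 0 to 6 months; only the handling of the recruitment visit is open.
- **That half of on-schedule women will be misclassified on attendance.** The 50% comes from centring a symmetric distribution on the cut-off, and applies only if the recruitment visit is excluded.

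**Conclusion.** The point holds for viral suppression and clinic attendance at month 3, and conditionally for oral-ART attendance at month 6.

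At month 3 the stated rules count a pre-intervention viral load as the outcome for any woman not seen again by then, and half of every woman's attendance window precedes randomisation. The share of women affected for viral load is about 17% to 84% for assumed mean gaps of 12 weeks to 3.25 months with SD 0.25 to 0.75 month. Because women are randomised, the carry-over should be similar in both arms, so the main consequence is dilution towards no difference rather than a bias favouring one arm.

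At month 6, a window sized for one visit sits against a two-visit rule. If the recruitment visit is excluded, about 9% to 92% of women keeping an approximately 3-monthly schedule would be scored as non-attenders under the same assumptions; if it counts, about 0%. The justification of securing one visit suggests that it is not counted, since visits at months 0 and 3 would already make two, but the article does not say so.

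Severity is moderate. The outcomes are tertiary and exploratory, and the trial's main conclusions do not rest on them.

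**What to change.** 1. **Viral suppression.** Define the month-3 and month-6 outcomes only from results obtained after the recruitment visit, in non-overlapping windows (for example, divided midway at 4.5 months). A woman with no result in a window is missing for that time point and is never given a baseline value.
2. **Attendance.** Apply the two-visit measure only over months 0 to 6 after baseline, not at month 3, and state that the recruitment visit is excluded.
3. **The month-6 boundary.** Either abstract records for about 1 to 2 further months, as a grace window for the second visit, or score attendance against scheduled visits. At a mean gap of 3 months (SD 0.25 to 0.75), one extra month cuts the share with fewer than two later visits from about 50% to 0–17%, and 1.5 extra months to 0–8%. At a mean gap of 3.25 months the corresponding shares are 8–32% and 0–17%.

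The exact limits are the study team's choice. What matters is that they are fixed in advance and exclude pre-intervention data.

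**Cost.** The change needs revised wording, somewhat later abstraction for the last recruits, and no added participant contact. There will be more missing values at month 3. If abstraction still stops at month 6, a separate late window will also lose women whose second visit comes afterwards. A longer period must match the EMR release and the consent description of abstraction, and may need ethics review, so it is best settled before the first participant is enrolled.
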